# The RECIPE study: reducing emergency Caesareans and improving the Primiparous experience: a blinded, prospective, observational study

**DOI:** 10.1186/s12884-020-03112-6

**Published:** 2020-07-29

**Keywords:** Caesarean delivery, Risk prediction, Model validation, Risk stratification, Personalised care

## Abstract

**Background:**

The RECIPE study aims to validate a risk prediction model for intrapartum caesarean delivery which has been developed by our group. The Genesis study was a prospective observational study carried out by the Perinatal Ireland Research Consortium across 7 clinical centres in Ireland between October 2012 and June 2015. Genesis investigated a range of maternal and fetal parameters in a prospective blinded study of 2336 singleton pregnancies between 39 + 0–41 + 0 weeks’ gestational age. This resulted in the development of a risk prediction model for Caesarean Delivery in nulliparous women at term. The RECIPE study now proposes to provide external validation of this risk prediction tool.

**Methods:**

In order to externally validate the model, we aim to include a centre which was not involved in the original study. We propose a trial of risk-assignment for intrapartum caesarean amongst nulliparous women with a singleton pregnancy between 38 + 0 and 40 + 6 weeks’ gestational age who are planning a vaginal birth. Results of the risk prediction tool will be concealed from participants and from midwives and doctors providing labour care.. Participants will be invited for an ultrasound scan and delivery details will be collated postnatally. The principal aim of this study is to externally validate the risk prediction model. This prediction model holds the potential to accurately identify nulliparous women who are likely to achieve an uncomplicated vaginal birth and those at high prospect of requiring an unplanned caesarean delivery.

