## Background

The OECD reports that Ireland has a Caesarean section rate of 28.5 per 100 live births [1].

The Irish National Maternity Strategy has highlighted the escalating Caesarean section rate as an area for concern and has identified Caesarean delivery as a key focus for change over the next ten years [2]. Of note, the Strategy also highlights the importance of reducing the rate of intrapartum caesarean delivery, owing to the heightened degree of both maternal and perinatal morbidity associated with unplanned Caesarean delivery performed during the course of labour. Postoperative complications, including haemorrhage and perioperative infection in women who undergo unplanned Caesarean delivery are significantly higher when compared to women who undergo elective Caesarean delivery.

Genesis [3] was a prospective, observational study carried out across seven clinical sites within the Perinatal Ireland Research consortium.

A total of 2336 nulliparous women were recruited to the study and underwent assessment at 39–41 weeks gestation that included an ultrasound scan and documentation of fetal and maternal anthropometric data. Delivery outcomes were subsequently collated.

Among 37 potential maternal, fetal, sociodemographic and obstetric factors studied, Genesis identified five key parameters (advancing maternal age, shorter maternal height, increasing BMI, larger fetal abdominal circumference and larger fetal head circumference) that represented the optimal prenatal predictive factors for intrapartum Caesarean section delivery in a composite model. A resultant algorithm was developed (the Genesis Risk Prediction Tool) as a means of providing a personalised risk assessment for Caesarean delivery in this population of nulliparous women with singleton uncomplicated pregnancies who were planning a vaginal birth [3]. The aim of the RECIPE study is to validate this prediction tool in a new population of women and to expand recruitment to include women from 38 + 0–41 + 0 weeks gestation. RECIPE will also recruit women from a new hospital site and include women who have pre-existing medical conditions which were excluded from Genesis.

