### Study design

This is a multicentre, blinded prospective observational study. All nulliparous singleton pregnancies with a cephalic presentation will be considered for enrolment. Exclusion criteria include women with a plan for caesarean delivery, multiple pregnancy, non-vertex presentation, known major fetal abnormality, uncertain gestational age, rupture of membranes or ultrasound-indicated reason for delivery at the time of ultrasound scan.

The study will be carried out in two clinical research sites-the Rotunda Hospital, Dublin and Our Lady of Lourdes Hospital, Drogheda. Recruitment will take place in the Rotunda Hospital Dublin from May 2017–March 2019 and in Our Lady of Lourdes Hospital, Drogheda from May 2018–March 2019. Both centres have tertiary-level neonatology facilities and the latter site includes a midwifery-led delivery unit.

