### Sample size calculation

Collins et al. have suggested that externally validating a prognostic model requires a minimum of 100 events coinciding with other approaches to externally validating predictive models for binary events [4]. Using this rationale, the sample size required is 500 nulliparous women, assuming a 20% intrapartum Caesarean section rate in the study population. The original Genesis study had a 21% intrapartum Caesarean section rate, with a similar cohort [3].

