### Data collection and analysis

Data management, data quality checks and statistical analysis will be performed by the trial biostatistician. The database will be anonymized, encrypted and stored in accordance with data protection law. Patient details will be recorded under an assigned study number, and access to the database will be password-protected to ensure access only by the study investigators.

The study will be analysed as a cohort to assess the accuracy of the Genesis predictive tool at identifying the women who will most likely require an intrapartum caesarean delivery as well as further analysis of the secondary objectives. The prediction model developed in the Genesis Study utilized a low-risk population, with a blinded third trimester ultrasound exam [3]. The exclusion criteria included: multiple pregnancy, non-vertex presentation, multiparous women, gestational age < 39 weeks, fetal abnormalities or aneuploidies, uncertain dates, pregnancy complications (e.g. growth restriction, pre-eclampsia) and pre-existing medical conditions (e.g. diabetes) and those considered for an elective caesarean section.

The Genesis prediction model [3] incorporated a third trimester EFW. Ultrasound EFW was accurate to within 10% of birthweight in 759 (87%) of patients and within 5% of birthweight in 428 (49%) of patients within 1 week of the delivery date.

This study is an external validation (specifically, spectrum transportability) of the prediction model in a population without a blinded third-trimester scan and who may be at an elevated risk for emergency cesarean section, compared to the original Genesis population. Model calibration and discriminative ability (e.g. AUC) will be assessed in this population. However, it is known that prediction models fitted with logistic regression often show poor performance when applied in populations other than the development population [5]. Since model updating may improve predictions, a closed-testing procedure will be used to update the prediction model [6]. This method balances the amount of evidence for updating the model in the new patient sample against the danger of overfitting.

The statistical packages SAS Version 9.4 and Stata Version 15 will be used to screen for outliers and anomalous values, tabulate, graphically summarize and model the data.

A CONSORT flow diagram can be viewed at Fig. 1.

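### The geographic part of the external-validation claim rests on one new centre, but the stated analysis and the 100-event minimum cover both sites together, so misfit at that centre can be diluted

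*Protocol article*

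**What the plan says.** The abstract (Methods) gives the design feature meant to deliver external validation: "In order to externally validate the model, we aim to include a centre which was not involved in the original study". The Background repeats it in the singular and lists it beside a change in case mix: "RECIPE will also recruit women from a new hospital site and include women who have pre-existing medical conditions which were excluded from Genesis".

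Study design names two hospitals: "The study will be carried out in two clinical research sites-the Rotunda Hospital, Dublin and Our Lady of Lourdes Hospital, Drogheda". Their windows differ: "Recruitment will take place in the Rotunda Hospital Dublin from May 2017–March 2019", and "in Our Lady of Lourdes Hospital, Drogheda from May 2018–March 2019". Neither is identified as the new one. The singular wording implies that the other took part in Genesis, but the article does not say so outright.

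The Sample size calculation relies on the rule that "externally validating a prognostic model requires a minimum of 100 events". It reaches 500 women at a 20% event rate for the study as a whole, with no figure per site.

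Under Data collection and analysis, "The study will be analysed as a cohort to assess the accuracy of the Genesis predictive tool". Calibration and AUC are to be assessed in the study population. The same section describes the work as external validation in the sense of spectrum transportability: the scan is unblinded and the women may be at higher risk than those in Genesis.

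**The concern.** The new centre is included to show that the model works in a hospital that did not help to build it. The article then describes no analysis that isolates that hospital, and it applies the event minimum to both sites together. Women from a hospital that supplied development data can show whether the model holds up later and in a broader case mix. They cannot show whether it transfers to another hospital.

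If the model is miscalibrated at the new centre, a pooled estimate averages that error with the result from the other hospital. The study could then report acceptable calibration and be read as evidence of transfer to new hospitals, although most of the data may come from a development site. The Discussion section and the abstract link validation to counselling individual women, to national relevance and to a later randomised trial. Those uses depend on the predicted risks being right in hospitals outside Genesis.

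**Working it through.** **1. The plan's own figure.** N = events / event rate = 100 / 0.20 = 500. This reproduces the article. At the 21% rate quoted for Genesis, 500 women would give 105 events.

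**2. Share of the new site.** Inputs from Study design: May 2017 to March 2019 is 23 calendar months; May 2018 to March 2019 is 11. Two assumptions are mine: the new site is the one with the 11-month window, and r is its monthly recruitment relative to the other's.

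Share s = 11r / (23 + 11r); women = 500s; events = 0.20 × 500s.

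| r | s | women | events |
|---|---|---|---|
| 0.5 | 5.5/28.5 = 0.193 | 96 | 19 |
| 1 | 11/34 = 0.324 | 162 | 32 |
| 2 | 22/45 = 0.489 | 244 | 49 |

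If the new site were instead the one with the 23-month window, equal monthly rates would give it 23/34 = 0.676, or about 338 women and 68 events. That is still below 100.

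**3. Dilution of misfit.** Take the observed/expected ratio (O/E) as 1.0 at the other site, with equal mean predicted risk at both sites (assumption). Then pooled O/E = (1 − s) × 1.0 + s × (O/E at the new site). With s = 0.324 and O/E = 1.5 at the new site: 0.676 + 0.324 × 1.5 = 1.16.

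The approximate standard error (SE) of O/E when calibration is correct is sqrt(0.2 × 0.8 / n) / 0.2:
- pooled, n = 500: 0.089, 95% half-width 0.18;
- new site, n = 162: 0.157, 95% half-width 0.31.

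A pooled O/E of 1.16 therefore lies within 1 ± 0.18. Approximate power is Φ(|O/E − 1| / SE − 1.96):

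| s | O/E at new site | pooled O/E | power, pooled | power, new site alone |
|---|---|---|---|---|
| 0.20 | 1.5 | 1.10 | 20% | 71% |
| 0.324 | 0.7 | 0.90 | 19% | 48% |
| 0.324 | 1.25 | 1.08 | 15% | 36% |
| 0.324 | 1.5 | 1.16 | 44% | 89% |
| 0.50 | 1.5 | 1.25 | 80% | 98% |

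In each scenario the new-site analysis has more power than the pooled one to see a fault confined to that site. The loss from pooling depends on the split.

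**4. Precision of the AUC (Hanley–McNeil, four non-events per event).** The article gives no AUC, so I assume 0.65 to 0.75. The 95% half-width is 0.059 to 0.063 with 100 events and 0.104 to 0.112 with 32.

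**The case against.** Four objections deserve an answer.

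*The claim has more than one basis.* A reader might infer from the abstract that external validation as a whole stands or falls with the new centre. The article does not support that. Data collection and analysis specifies spectrum transportability, the eligible population is wider than in Genesis, and recruitment (2017 to 2019) is later than the Genesis period (2012 to 2015). Women at the other hospital contribute to those aims. This objection stands, and it confines the point to geographic transfer.

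*Results by site may be planned elsewhere.* A reader might infer that none are planned. The article says only that the study is analysed as a cohort, which could partly describe the study type, and an analysis plan that is not shown could add them. This also stands: none is stated, which does not mean that none exists. What remains is a mismatch within the article itself, where a new centre is given as the route to validation while the event target and the described analysis do not distinguish it.

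*The split is unknown.* It is tempting to say that two thirds of the information comes from a development hospital. That needs equal monthly recruitment and the shorter-window site to be the new one, and the article states neither. Hence the range above.

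*Site results would be imprecise.* With about 162 women, an O/E of 1.25 would be detected with only 36% power, so reporting by site will not settle moderate misfit. That is true, but it is a reason to word the geographic claim cautiously. It does not justify letting a pooled estimate stand in for it.

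**Conclusion.** The point holds for the geographic part of the claim. The article ties external validation partly to one centre outside Genesis, yet it describes a single-cohort analysis and an event minimum that only the two sites together are sized to meet. Poor fit at the new centre can be diluted: an O/E of 1.5 there against 1.0 at the other site pools to about 1.16 at a 32% share, with 44% power pooled against 89% at the new site alone.

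The size rests on assumptions that the article does not settle: that the 11-month site is the new one, that its monthly recruitment is 0.5 to 2 times the other's (about 19 to 49 events), that the 20% event rate applies at both sites, and that mean predicted risk is equal at both. If the split were even, the same fault would be found in the pooled data with 80% power.

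A reader might also infer that the sample size is wrong. It is not: 500 follows from the stated rule. A larger study would be needed only if the new centre alone had to carry the validation.

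**What to change.** - State which hospital was not in Genesis, and how many women and events are expected there.
- Report AUC, O/E and calibration slope with 95% confidence intervals for each site as well as pooled, and fit site-specific calibration intercepts in the pooled analysis.
- Limit the geographic external-validation claim to the new-site estimate. Describe the other hospital's result as temporal and case-mix validation.
- State that the 100-event minimum is met only by the pooled data, so the new-site result is an estimate with its uncertainty and not a test passed.

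This takes a few lines of analysis and text and no extra recruitment. The drawback is that wide new-site intervals become visible (at about 32 events, roughly ±0.31 on O/E and ±0.11 on AUC) and the geographic claim becomes weaker.

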**Discussion:**

Validation of the Genesis prediction model would enable more accurate counselling for women in the antenatal setting regarding their own likelihood of requiring an intrapartum Caesarean section. It would also provide valuable personalised information to women about the anticipated course of their own labour. We believe that this is an issue of national relevance that will impact positively on obstetric practice, and will positively empower women to make considered, personalised choices surrounding labour and delivery.

## Background

The OECD reports that Ireland has a Caesarean section rate of 28.5 per 100 live births [1].

The Irish National Maternity Strategy has highlighted the escalating Caesarean section rate as an area for concern and has identified Caesarean delivery as a key focus for change over the next ten years [2]. Of note, the Strategy also highlights the importance of reducing the rate of intrapartum caesarean delivery, owing to the heightened degree of both maternal and perinatal morbidity associated with unplanned Caesarean delivery performed during the course of labour. Postoperative complications, including haemorrhage and perioperative infection in women who undergo unplanned Caesarean delivery are significantly higher when compared to women who undergo elective Caesarean delivery.

Genesis [3] was a prospective, observational study carried out across seven clinical sites within the Perinatal Ireland Research consortium.

A total of 2336 nulliparous women were recruited to the study and underwent assessment at 39–41 weeks gestation that included an ultrasound scan and documentation of fetal and maternal anthropometric data. Delivery outcomes were subsequently collated.

Among 37 potential maternal, fetal, sociodemographic and obstetric factors studied, Genesis identified five key parameters (advancing maternal age, shorter maternal height, increasing BMI, larger fetal abdominal circumference and larger fetal head circumference) that represented the optimal prenatal predictive factors for intrapartum Caesarean section delivery in a composite model. A resultant algorithm was developed (the Genesis Risk Prediction Tool) as a means of providing a personalised risk assessment for Caesarean delivery in this population of nulliparous women with singleton uncomplicated pregnancies who were planning a vaginal birth [3]. The aim of the RECIPE study is to validate this prediction tool in a new population of women and to expand recruitment to include women from 38 + 0–41 + 0 weeks gestation. RECIPE will also recruit women from a new hospital site and include women who have pre-existing medical conditions which were excluded from Genesis.

## Methods/design

The primary objective of the RECIPE study is to externally validate the Genesis predictive risk tool to examine if it can accurately predict the need for emergency caesarean section delivery in nulliparous women.

Secondary objectives include validation in an extended obstetric population, to enumerate maternal or neonatal complications and to ascertain women’s satisfaction with their labour experience with a postnatal interview.

### Study design

This is a multicentre, blinded prospective observational study. All nulliparous singleton pregnancies with a cephalic presentation will be considered for enrolment. Exclusion criteria include women with a plan for caesarean delivery, multiple pregnancy, non-vertex presentation, known major fetal abnormality, uncertain gestational age, rupture of membranes or ultrasound-indicated reason for delivery at the time of ultrasound scan.

The study will be carried out in two clinical research sites-the Rotunda Hospital, Dublin and Our Lady of Lourdes Hospital, Drogheda. Recruitment will take place in the Rotunda Hospital Dublin from May 2017–March 2019 and in Our Lady of Lourdes Hospital, Drogheda from May 2018–March 2019. Both centres have tertiary-level neonatology facilities and the latter site includes a midwifery-led delivery unit.

### Study procedures

#### Antenatal clinical assessment and ultrasound scan

Maternal demographic and anthropometric details will be collected at the scheduled appointment with the research sonographer.

A fetal ultrasound scan will be performed to obtain fetal biometry at a gestational age of 38 + 0–41 + 0 weeks.

Fetal biometry will include the following parameters: Fetal Head Circumference (HC), Bi-Parietal Diameter (BPD), Abdominal Circumference (AC) and Femur Length (FL). The Estimated Fetal Weight (EFW) will be obtained using the Hadlock-4 formula (HC, BPD, AC, FL). EFW will be freely available to women and clinicians and this differs from the Genesis study where these details were blinded in order to reduce bias.

Fetal biometry and amniotic fluid volume will be reported to the patient and care providers, however the individualized calculated risk for requiring an intrapartum cesarean delivery will be determined post-patient encounter/ ultrasound and will be concealed from the participants, midwives and clinicians..

In the event of an abnormal scan finding, the ultrasonographer will contact the patient’s obstetric team and that woman will be excluded from the study.

Abnormal scan findings which would necessitate such exclusion include the following: Ultrasound-indication for delivery at time of recruitment scan (Fetal growth restriction <3rd percentile, biophysical profile </=4/8, oligohydramnios DVP (Deepest Vertical Pool) < 2 cm).

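### A tool built on scans from 39+0 is applied to scans from 38+0 and assessed in one pooled cohort, so scan timing can be mistaken for a population difference

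*Protocol article*

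**What the plan says.** - **Scan window.** The section on antenatal clinical assessment and ultrasound scan states: "A fetal ultrasound scan will be performed to obtain fetal biometry at a gestational age of 38 + 0–41 + 0 weeks". The individual risk is calculated after that visit, and no later scan or projection is described. The Methods part of the abstract ends the window a day earlier: "singleton pregnancy between 38 + 0 and 40 + 6 weeks". The Background gives 41+0.
- **Development data.** The abstract describes Genesis as "2336 singleton pregnancies between 39 + 0–41 + 0 weeks’ gestational age". The exclusions listed under Data collection and analysis include "multiple pregnancy, non-vertex presentation, multiparous women, gestational age < 39 weeks".
- **Predictors.** The Background lists "advancing maternal age, shorter maternal height, increasing BMI, larger fetal abdominal circumference and larger fetal head circumference". Gestational age is not among them, and the scale of the two circumferences is not given.
- **Analysis.** Data collection and analysis treats the women as one cohort, with calibration, AUC and a closed-testing update. It names two differences from Genesis, the unblinded scan and possibly higher-risk women. It does not name the earlier scan window, although the Background makes the extension to 38+0 an explicit aim.

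**The concern.** HC and AC change as the fetus grows, while the tool as described does not know when the scan was done. Genesis contained no scans before 39+0, so applying the tool at 38+0–38+6 extrapolates in time. If the circumferences enter as raw size, the same fetus scanned a week earlier has smaller values and a lower predicted risk.

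Calibration is one of the two stated performance measures. In a pooled cohort, under-prediction caused by early scans looks the same as under-prediction caused by a higher-risk population. The update step would then correct for a population difference that is partly scan timing. The Discussion intends a validated tool to lead to a randomised trial.

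**Working it through.** **1. The plan's own figure.** The sample size is events divided by event rate: 100 / 0.20 = 500. It reproduces, and nothing below changes it.

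**2. Inputs.** From the article: the Genesis window 39+0–41+0, the RECIPE window 38+0–41+0, positive directions for HC and AC, no gestational-age term, and a caesarean rate of 20%. Not in the article, and therefore assumed: odds ratios per 10 mm, growth per week, and entry of HC and AC as raw size.

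**3. Shift for a scan one week earlier.** On the log-odds scale, k = ln(OR_HC) × HC growth/10 + ln(OR_AC) × AC growth/10, with growth in mm per week. A 20% risk becomes expit(logit(0.20) − k).

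| Case | OR HC, AC | Growth HC, AC | k | 20% becomes |
|---|---|---|---|---|
| Low | 1.1, 1.05 | 1, 5 | 0.034 | 19.5% |
| Middle | 1.3, 1.15 | 2.5, 7.5 | 0.170 | 17.4% |
| High | 1.5, 1.3 | 4, 10 | 0.425 | 14.1% |

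With zero growth the shift is zero. If the inputs were standardised for gestation, it would largely disappear.

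**4. Calibration and AUC.** Two million women were simulated per case. The linear predictor at 40+0 was normal (mean −1.55, SD 0.75, about 20% events), scans were spread evenly over the window, and true risk did not depend on scan week.

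| Case | O/E, 39–41 | O/E, 38–41 | O/E, 38–39 | AUC, 39–41 to 38–41 |
|---|---|---|---|---|
| Low | 1.00 | 1.01 | 1.04 | 0.694 to 0.694 |
| Middle | 1.00 | 1.06 | 1.21 | 0.692 to 0.690 |
| High | 0.99 | 1.14 | 1.63 | 0.685 to 0.674 |

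**5. What an intercept update does.** With even scans over 38–41 the mean gestation is 39.5, half a week before the 40+0 reference. The intercept therefore rises by about 0.5k. Scans at 38–39 (mean 38.5) were low by 1.5k and stay low by 1.5k − 0.5k = k. Scans at 39–41 (mean 40) were unbiased and become too high by 0.5k. In the middle case that is 0.17 too low and 0.085 too high on the log-odds scale. A slope b multiplies the dependence on scan week to b × k but does not remove it.

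**6. Precision of a split.** About 100 events spread evenly over three weeks give about 33 per week. The 95% limits for O/E are the estimate divided and multiplied by exp(1.96 × √(0.8/33)) = 1.36. An O/E of 1.04 has limits 0.77–1.41, 1.21 has 0.89–1.64, and 1.63 has 1.20–2.21. Only the high case would stand clear of 1.

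**The case against.** The strongest objection is that the decisive fact is not in the article. The equation belongs to the cited development study, and if HC and AC were standardised for gestation the problem would largely go. This stands as a condition. The Background describes "larger fetal abdominal circumference and larger fetal head circumference", for which raw size is the natural reading, but the scale is not stated. Data collection and analysis also says that the model used an estimated fetal weight, which the five-predictor list does not contain. Raw weight would depend on timing in the same way.

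Second, the extension to 38+0 is declared, and applying a tool unchanged is what external validation means. This stands too. The criticism is not of the extension, but of pooling across it when the development boundary is known.

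Third, detailed subgroup tables usually belong in an analysis plan. That is fair, but the article does set out how this population differs from Genesis and leaves this difference out.

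A reader might infer more than the article supports:
- **That every prediction is biased.** Genesis already spanned two weeks, so that spread is inside its coefficients. The new exposure is mainly 38+0–38+6.
- **That discrimination will suffer materially.** The simulated loss is 0.000 to 0.011.
- **That under-prediction is certain.** Women scanned at 38 weeks include some who deliver that week, and they could not have entered Genesis. True risk may differ by scan week, whereas the simulation holds it fixed.
- **That the fetal-weight accuracy figures are misapplied.** The article already limits them to scans "of patients within 1 week of the delivery date", and they say nothing direct about HC or AC.

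**Conclusion.** The point holds as a limited one about calibration and updating. The tool was developed from 39+0 without a gestational-age term, and RECIPE applies it from 38+0 and pools the women. If the circumferences enter as raw size, and true risk does not itself vary with scan week, 38-week scans tend to be under-predicted. A pooled intercept or slope update averages over that effect without removing it.

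The size ranges from trivial to large and cannot be settled from the article, because both the growth rates and the odds ratios are assumed. The case for acting is that the remedy is cheap and bears on the primary objective, not that serious miscalibration has been shown. The difference between 40+6 and 41+0 is a one-day editorial inconsistency and does not support the main point.

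**What to change.** 1. State the scale on which HC and AC enter the tool. If they are standardised for gestation, saying so largely closes the point.
2. Report calibration (observed/expected, intercept and slope) separately for scans at 39+0 or later, which is the Genesis window, and for scans at 38+0–38+6.
3. Test gestational age at scan as an added term in the closed-testing update.
4. Projecting HC and AC to a reference gestation can be an optional sensitivity analysis only. It relies on an assumed growth standard and in effect tests a different tool.
5. Do not make stratification by scan-to-delivery interval a main analysis, because the interval is unknown when the prediction is made.
6. Reconcile the upper limit of the window between the abstract and the body of the article.

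Gestation at scan is needed for eligibility, so no new data are required and the sample size of 500 stands. The costs are analysis time, one degree of freedom for the added term, and imprecise split estimates. With about 33 events in the 38-week group, those estimates should be presented as descriptive.
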